**LIST OF ABBREVIATIONS AND RELEVANT DEFINITIONS**

|                |                                                                                                                                                                                                                                                                                                                                                  |
|----------------|--------------------------------------------------------------------------------------------------------------------------------------------------------------------------------------------------------------------------------------------------------------------------------------------------------------------------------------------------|
| ABR     | ABR form, General Assessment and Registration form, is the application form that is required for submission to the accredited Ethics Committee (In Dutch, ABR = Algemene Beoordeling en Registratie)                                                                                                                                      |
| AE      | Adverse Event                                                                                                                                                                                                                                                                                                                             |
| CCMO    | Central Committee on Research Involving Human Subjects; in Dutch: Centrale Commissie Mensgebonden Onderzoek                                                                                                                                                                                                                               |
| CV      | Curriculum Vitae                                                                                                                                                                                                                                                                                                                          |
| EU      | European Union                                                                                                                                                                                                                                                                                                                            |
| IC      | Informed Consent                                                                                                                                                                                                                                                                                                                          |
| METC    | Medical research ethics committee (MREC); in Dutch: medisch ethische toetsing commissie (METC)                                                                                                                                                                                                                                            |
| Sponsor | The sponsor is the party that commissions the organisation or performance of the research, for example a pharmaceutical company, academic hospital, scientific organisation or investigator. A party that provides funding for a study but does not commission it is not regarded as the sponsor, but referred to as a subsidising party. |
| WMO     | Medical Research Involving Human Subjects Act (in Dutch: Wet Medisch-wetenschappelijk Onderzoek met Mensen)                                                                                                                                                                                                                               |

## SUMMARY

**Rationale:** There is growing consensus that targeting negative symptoms such as social withdrawal is essential to be able to preserve social participation, thereby reducing the high yearly costs of schizophrenia. Aaron T. Beck, founder of Cognitive Behavioural Therapy (CBT), and colleagues have developed and investigated a new CBT approach, in which they target inactivity in a chronic schizophrenia population with severe negative symptoms. The therapy is based on accumulating evidence that dysfunctional beliefs in conjunction with neurocognitive impairments can impede social functioning. These results suggest that CBT can be highly successful in establishing clinically meaningful improvements. However, the therapy has not yet been investigated in a recent-onset population.

**Objective:** To evaluate the applicability and (cost-) effectiveness of a shortened, partly group based, Cognitive Behavioural Therapy focussing on social activation (CBTsa) in patients with recent onset schizophrenia.

**Hypotheses:** 1) We hypothesize that CBT focused on social activation (CBTsa) in a recent-onset population will result in a substantial reduction in severity of negative symptoms, in particular social withdrawal.

2) We expect that CBTsa will lead to an improvement in terms of Quality of Life and overall functioning.

3) We expect this intervention to result in a reduction in need for care and QALY gain as a consequence of improvement in symptoms and social functioning.

**Study design:** Single blind randomized controlled trial with 6 month-follow up.

**Study population:** Patients between 18 and 35 years old with negative symptoms of at least moderate severity, and who have been recently (< 2yrs) diagnosed with schizophrenia.

**Intervention (if applicable):** Individual and group-based CBT intervention targeting social withdrawal.

**Main study parameters/endpoints:** Change in negative symptoms, Social functioning, and quality of life, Productivity losses.

**Nature and extent of the burden and risks associated with participation, benefit and group relatedness:** Burden: Patients will undergo a 2-hour during structured interview and will carry along a mobile device with which participants are prompted by a beep at random intervals throughout the day (for a 6-day period) to report about their current experiences and withdrawal behaviour. These assessments will be repeated post-treatment and at 6-month follow-up. Risks: No risks are attached to this study. Benefits: With this intervention early in the course of the disorder we hope a) to prevent social withdrawal and diminish negative symptoms, thereby preventing the young patient from dropping-out of his/her social roles and from early social exclusion and/ or b) to help regain social roles when drop-out already occurred.

## INTRODUCTION AND RATIONALE

### Scientific rationale

Poor social functioning is a severely disabling characteristic of schizophrenia. It is more persistent over time than positive symptoms and despite antipsychotic treatment, functional prognosis has remained generally poor [1]. An important aspect of poor social functioning is the tendency to withdraw from social contact, one of the 'negative symptoms' of schizophrenia. There is growing consensus that targeting negative symptoms such as social withdrawal is essential to be able to preserve social participation [2]; thereby reducing the high yearly costs of schizophrenia.

Aaron T. Beck, founder of Cognitive Behavioural Therapy (CBT), and colleagues have developed and investigated a new CBT approach, in which they target inactivity in a chronic schizophrenia population with severe negative symptoms; a subgroup that has always believed to be highly treatment resistant. The therapy is based on accumulating evidence that dysfunctional beliefs in conjunction with neurocognitive impairments can impede functioning [3]. Its primary focus is to help patients overcome isolation and inactivity, thereby improve quality of life [2], rather than primarily focussing on the reduction of psychotic symptoms. Grant, Beck and colleagues [3] found that patients treated with CBT not only showed more improvement in global functioning than patients in the Standard Treatment condition, they also showed a greater reduction in avolition/apathy and psychotic symptoms. These results suggest that CBT can be highly successful in establishing clinically meaningful improvements.

Thus far, this intervention has only been investigated in patients with chronic schizophrenia although there is increasing evidence that social withdrawal is also prominent in the early phase of the illness. Moreover, there is growing consensus that early intervention is more effective in improving illness course than intervention at a later stage of the illness [4]. In the present study we aim to examine whether a relatively short, partly group based CBT targeting negative symptoms in recent-onset schizophrenia patients results in reduced social withdrawal, need for care and improvement in quality of life and in overall functioning compared to treatment as usual.

### Clinical Relevance

We expect that intervening early is more effective in improving social integration than at a later stage when dysfunctional behaviours have become embedded in a fixed pattern of behaviour. We anticipate that this intervention will result in substantial gains regarding negative symptoms, and in particular social withdrawal. Intervening in this early phase of the illness is expected to a) prevent the young patient from dropping-out of his/her social roles

and from early social exclusion and/ or b) to help regain social roles when drop-out already occurred.

#### Anticipated Cost-Effectiveness/ Budget Impact

A secondary aim of the present study is to examine the cost-effectiveness of this new type of intervention. We based our estimated cost-effectiveness on the following calculation:

1. Costs of the intervention per patient are estimated at 800 Euro.
2. We expect a reduction in negative symptoms with an effect size of .66 compared to standard care only [3].
3. There is a small effect or no effect of usual care on negative symptoms [3&5]. Since the exact effect is unclear and our concern is the additional effect, we set the effect of usual care at 0, and use the effect of our intervention (effect size 0,66) compared to usual care. Assuming that negative symptoms resemble depression, and that negative symptoms persist half a year, this amounts to a QALY gain of  $0,66 \text{ (effect size)} \times 0,172 \text{ (conversion factor d->dw)} \times 0,5 \text{ (duration of half a year)} \text{ per patient} = 0.057$ .
4. The costs for an additional QALY then are  $800/0,057 = \text{€}14.035,09$  per additional QALY.
5. This is below the €20.000 cut-off, as a result of which the intervention may be considered costeffective

#### Existing evidence of effectiveness

In a recently finished pilot study of our research group [6], 21 patients (of which 4 recent-onset) were treated in a RCT trial based on the principles of the Grant et al. [3] study. The researchers concluded the following:

- (1) Feasibility of the treatment and treatment manual was good,
- (2) Positive effects: Intention-to-treat analyses showed a within group effect size of 1.26 on negative symptoms ( $t=6.16$ ,  $| \text{sig}=.000$ ); and
- (3) the recent-onset patients showed a greater reduction in negative symptoms than the chronic schizophrenia population.

#### Innovative character

To the best of our knowledge, no other study has examined the applicability of a concise version of the CBT as developed by Grant et al in a recent-onset population. Notwithstanding the highlighted advantages of the CBT intervention in chronic schizophrenia, a main drawback is its rather long duration (18 months on a weekly basis), bringing along substantial costs. We have developed a shorter, partly group-based intervention, adapted to the specific needs of this young group in the early stage of the illness. We expect this adapted approach to be more feasible and cost-effective compared to the original intervention.

## 1. OBJECTIVES

### Primary Objective:

The primary aim of this project is to examine a shortened (+/- 20 sessions) and partly group-based version of the new and promising CBT approach tested in a chronic population (from now: 'Cognitive Behavioural Therapy – Social Activation' (CBTsa)), for its applicability and effectiveness in a recent-onset population. The CBTsa will be adjusted to the specific needs of the young recent-onset cohort.

### Secondary Objective(s):

We secondly aim to explore the cost-effectiveness of this new intervention (i.e. the balance between costs and health outcomes for CBTsa compared with treatment as usual(ST)).

### Hypotheses:

- 1) We hypothesize that CBT focused on social activation (CBTsa) will result in a substantial reduction in severity of negative symptoms, and in particular social withdrawal.
- 2) We expect this intervention to result in a reduction in need for care and QALY gain as a consequence of improvement in symptoms and social functioning.
- 3) We expect that CBTsa will lead to an improvement in terms of Quality of Life and overall functioning and symptomatology.

## **STUDY POPULATION**

### **2.1 Population (base)**

Study sample: patients hospitalized or attending day-treatment or receiving outpatient care at the Department of Early Psychosis, Amsterdam, Early Intervention Psychosis service of Arkin, Amsterdam (Vroege Interventie Psychose: VIP) the psychosis department of the ABC team, Utrecht and Centrum First Psychosis, Parnassia, The Hague. To maximise engagement, group therapy will be presented as part of the standard dayprogram. Individual therapy sessions will be delivered flexibly (time, location). All participants are embedded within a low-threshold intensive outreaching care system (aligned with our academic department).

### **2.2 Inclusion criteria**

In order to be eligible to participate in this study, a subject must meet all of the following criteria:

- (1) recent onset schizophrenia or related disorder (start antipsychotic medication <2 yr);
- (2) Social withdrawal (> 3 moderate severity on the PANSS N4; Passive/apathic social withdrawal; range 0-7);
- (3) Aged 18-35 years;
- (4) Fluent in Dutch
- (5) IQ>70;
- (6) Able and willing to give informed consent

### **2.3 Exclusion criteria**

A potential subject who meets any of the following criteria will be excluded from participation in this study:

- (1) Younger than eighteen years of age;
- (2) No mastery of the Dutch language;
- (3) Negative symptoms as a consequence of positive symptoms (e.g. withdrawal due to paranoid delusions). Positive symptoms as such are not an exclusion criterion; only when they are considered to be the primary cause of the negative symptoms, in which case CBT focused on positive symptoms or another type of intervention for positive symptoms is called for.

### **2.4 Sample size calculation**

The effectsize to calculate our estimated sample size is based upon a recent groundbreaking study of Grant and colleagues (one of our co-applicants), who carried out an intervention with

similar ingredients as ours in a more chronic schizophrenia population. In their study, also specifically targeted to reduce negative symptoms and to socially activate their patient sample, they found that patients receiving cognitive therapy showed a greater mean reduction in avolition-apathy (adjusted mean [SE], 1.66 [0.31] vs 2.81 [0.34], respectively;  $P=.01$ ; between-group  $d=-0.66$ ) as compared with those receiving standard treatment. This outcome measure is comparable to the 'social withdrawal' outcome measure used in our study. Based on this results, and upon the commonly hold assumption that recent onset subjects are more likely to change than the more chronic population, we estimated to find an effectsize of (at least) .66 in our study as well. With an alpha of 0.5; power=80%; effect-size .66 [3], this would mean we need 36 participants per group to detect a true treatment difference. Taking into account an expected dropout rate of 20%, we would need to include  $72 + 20\% = 87$  participants = 44 per group.

To take into account the 'variance inflation' factor (due to our multi-center design), we calculated the Intra Class Correlation Coefficient of the PANSS negative symptom scores of a study targeting a similar population and setting (GROUP), in which 4 centers participated. The ICC in this study was .146. Following the literature, we then used the following formula:  
 $1 + (m-1) \times \text{ICC}$  (m= number of participating centers).

For our study this means we have to increase the sample size (87) by a factor of:

$$1 + (3-1) \times .146 = 1.292$$

This results in a total estimated sample size of:  $1.292 \times 87 = 112$  individuals (56 per condition)

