### **4.4 Replacement of individual subjects after withdrawal**

Dropout has been factored in at the sample size calculation. As we start treatment at group-level, individual subjects will not be replaced after withdrawal.

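### Section 2.4 misprints the significance level as 0.5 and adds 20% for dropout instead of dividing by 0.8, so its chain should reach 117 rather than 112

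*Protocol*

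**What the plan says.** Protocol section 2.4 (Sample size calculation) takes its effect size from an earlier trial in chronic patients: "we estimated to find an effectsize of (at least) .66 in our study as well". It then states "With an alpha of 0.5; power=80%; effect-size .66 [3], this would mean we need 36 participants per group". It does not say whether the test is one- or two-sided.

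The next step is dropout: "Taking into account an expected dropout rate of 20" per cent, the section adds 20% to 72 and reaches 87, or 44 per group. Finally it multiplies 87 by a variance inflation factor of 1.292, formed from an ICC of .146 and three centres, and arrives at 112 (56 per condition).

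Two other places bear on this. Section 4.4 (Replacement of individual subjects after withdrawal) relies on the dropout step, "Dropout has been factored in at the sample size calculation", and rules out replacement. Section 5.3, which describes the primary analysis, gives no significance level.

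**The concern.** The sample size should be reproducible from its stated inputs, and here it is not. A reader who enters alpha 0.5 does not get 36 per group. Because no other significance level appears in the protocol, the only prespecified threshold is ten times the one evidently used.

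The dropout step has a different fault. A 20% dropout rate applies to the people enrolled, so the number to enrol is the number of completers needed divided by 0.8. Adding 20% to the completers gives a smaller number, and the error carries into the final total. Since withdrawn participants are not replaced, nothing later in the plan makes up the difference.

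At stake are the accuracy of the stated threshold and a modest overstatement of the power that the plan's own assumptions give.

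**Working it through.** **Inputs, all from section 2.4:** d = 0.66, power 80%, alpha printed as 0.5, 36 per group (72 in total), equal arms, dropout 20%, inflation factor 1 + (3 − 1) × 0.146 = 1.292, final N 112.

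**Step 1: reproduce 36 per group.** Normal formula: n per group = 2 × (z for alpha + z for power)² / d², with z for 80% power = 0.8416 and d² = 0.4356.

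| Alpha | Sides | n per group |
|---|---|---|
| 0.5 (as printed) | two | 10.55, so 11 (9.9 by t-test) |
| 0.5 (as printed) | one | 3.25, so 4 |
| 0.05 | one | 28.39, so 29 |
| 0.05 | two | 2 × (1.96 + 0.8416)² / 0.4356 = 36.04 |

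Only two-sided 0.05 gives the stated 36. (One-sided 0.025 is the same calculation.) At alpha 0.5, 36 per group would have 98% power.

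**Step 2: dropout.**
- The plan: 72 × 1.2 = 86.4, rounded up to 87.
- Expected completers from 87: 87 × 0.8 = 69.6. From 44 per group: 88 × 0.8 = 70.4. Both are below 72.
- Correct step: 72 / 0.8 = 90, or 45 per group.

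**Step 3: carry through the plan's own factor.**
- The plan: 87 × 1.292 = 112.4, stated as 112.
- Corrected: 90 × 1.292 = 116.3, so 117, or 118 for equal arms. The stated target is 5 below 117.

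**Step 4: power at 112 enrolled, two-sided 0.05.** Expected completers: 112 × 0.8 = 89.6. Normal formula: power = Φ(0.66 × √(n/2) − 1.96), with n per group.

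| Case | n per group | Normal formula | t-test |
|---|---|---|---|
| What the plan intends | 36 | 80.0% | 78.9% |
| 112 enrolled, factor 1.292 needed in full: 89.6 / 1.292 = 69.35 effective completers | 34.67 | 78.5% | 77.3% |
| 112 enrolled, factor not needed | 44.8 | 87.8% | 87.1% |

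With the factor, the dropout error costs 80.0 − 78.5 = 1.5 points by the normal formula, the one that reproduces 36. The t-test figure of 77.3% should be compared with its own 78.9%, not with 80%.

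**The case against.** The case for leaving this alone is that both errors are editorial. The 36 printed beside alpha 0.5 shows that the calculation was run at two-sided 0.05, and the final testing level may be set in an analysis plan that is not shown. The trial enrols 112, not 87, so it expects 89.6 actual completers, well above 72. Section 4.5 asks participants who withdraw to attend follow-up assessments, and the mixed model of section 5.3 can use partial data, so treating every dropout as a complete loss is the worst case.

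Most of this stands, and it rules out three stronger readings that a reader might infer:

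- *That the alpha of 0.5 weakens the trial.* It does not. Taken literally it would raise power, and as a misprint it leaves the 36 per group untouched.
- *That the trial will have fewer than 72 completers or is underpowered.* The shortfall below 72 is in effective completers, after division by 1.292. That factor is itself open to question: section 2.4 sets m to the number of centres, while section 4.2 randomises patients within each centre. If it is not needed, power at 112 exceeds 80%.
- *That 36 should have been 37.* Rounding 36.04 to 36 gives 79.96% by the formula used, which is not an error worth raising.

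The objection does not remove the two wrong figures. A separate analysis plan would not make a wrong alpha in the protocol right, and 72 plus 20% does not leave 72 after a 20% loss.

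**Conclusion.** Section 2.4 contains two wrong figures. The printed alpha of 0.5 is a misprint for two-sided 0.05. It affects neither completers nor power, but it is the only significance level in the protocol. The dropout step gives 87 where 90 is needed, so the plan's own chain should end at 117 (118 for equal arms) instead of 112.

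The size is small: about 1.5 points of power by the normal formula, from 80.0% to 78.5%, if the 1.292 factor is needed in full. This rests on d = 0.66, 20% dropout counted as complete loss, two-sided 0.05 and a two-group comparison of means, not on the planned mixed model. If the factor does not apply, 112 gives about 87 to 88%. A loss of the planned 80% power is therefore not demonstrated. The arithmetic of both errors is certain; the actual power depends on the centre factor.

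**What to change.** In section 2.4:

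1. Replace alpha 0.5 with two-sided alpha 0.05.
2. Replace 72 + 20% = 87 (44 per group) with 72/0.80 = 90 (45 per group).
3. Show the corrected end of the chain, 90 × 1.292 = 116.3, so 117 (118 for equal arms).
4. Keep 112 (56 per condition) as the enrolment target, and say plainly that it is below the 117 the corrected chain gives. Without this sentence, changing 87 to 90 would leave the section unable to arrive at its own total.
5. State the power at 112: about 78.5% by the normal formula (77.3% by t-test) under the 1.292 factor, or about 87 to 88% if that factor is found not to apply given randomisation within centre.

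The cost is a text correction, with no change to enrolment or procedures. The downside is that the stated power under the plan's own factor becomes about 1.5 points less favourable.
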